## Abstract

**Background:**

Open discectomy is the standard surgical procedure in the treatment of patients with long-lasting sciatica caused by lumbar disc herniation. Minimally invasive approaches such as microendoscopic discectomy have gained attention in recent years. Reduced tissue trauma allows early ambulation, short hospital stay and quick resumption of daily activities. A comparative cost-effectiveness study has not been performed yet. We present the design of a randomised controlled trial on cost-effectiveness of microendoscopic discectomy versus conventional open discectomy in patients with lumbar disc herniation.

**Methods/Design:**

Patients (age 18–70 years) presenting with sciatica due to lumbar disc herniation lasting more than 6–8 weeks are included. Patients with disc herniation larger than 1/3 of the spinal canal diameter, or disc herniation less than 1/3 of the spinal canal diameter with concomitant lateral recess stenosis or sequestration, are eliglible for participation. Randomisation into microendoscopic discectomy or conventional unilateral transflaval discectomy will take place in the operating room after induction of anesthesia. The length of skin incision is equal in both groups. The primary outcome measure is the functional assessment of the patient, measured by the Roland Disability Questionnaire for Sciatica, at 8 weeks and 1 year after surgery. We will also evaluate several other outcome parameters, including perceived recovery, leg and back pain, incidence of re-operations, complications, serum creatine kinase, quality of life, medical consumption, absenteeism and costs. The study is a randomised prospective multi-institutional trial, in which two surgical techniques are compared in a parallel group design. Patients and research nurses are kept blinded of the allocated treatment during the follow-up period of 2 years.

**Discussion:**

Currently, open discectomy is the golden standard in the surgical treatment of lumbar disc herniation. Whether microendoscopic discectomy is more cost-effective than unilateral transflaval discectomy has to be determined by this trial.

## Background

Sciatica due to lumbar disc herniation refractory to conservative treatment is effectively treated by surgery. The primary goal of surgery is retrieval of herniated disc fragments and decompression of the nerve root. Since the first report of lumbar disc surgery in 1934 by Mixter and Barr [1], who performed a laminectomy with transdural disc removal, various less invasive techniques have been developped. With the introduction of the microscope, Yasargil and Caspar refined the original laminectomy into the open microdiscectomy [2,3]. This technique has become the most common procedure worldwide. In 1997 Foley and Smith introduced the transmuscular approach of microendoscopic discectomy (MED) with advanced optics and instruments applicated in laparoscopic surgery [4]. Later, the original endoscopic procedure was modified with the operative microscope which has led to the development of the Microscopic Endoscopic Tubular Retractor System (METRX). This technique is subject of our protocol.

The concept of minimally invasive spine surgery is less tissue damage, while achieving good clinical outcome comparable with conventional open surgery. Patients are expected to have less back pain, shorter hospitalisation and quicker resumption of daily activities. Moreover, the cost-effectiveness is expected to be superior.

The Cochrane review of lumbar disc surgery has shown considerable evidence on the effectiveness of discectomy in patients in whom conservative management has failed [5]. Three studies compared microdiscectomy versus standard open discectomy [6-8]. Use of the microscope lengthened the surgical procedure but there was no significant difference in clinical outcome. The expected earlier return to work was not realised. This could be explaned by the rather small difference in invasiveness between microdiscectomy and the frequently performed unilateral transflaval approach by using loupe magnification. Nowadays, these two procedures are lumped together. A randomised controlled trial (RCT) between microdiscectomy with microscope versus microdiscectomy with loupe magnification has not been performed.

The Cochrane review did not include trials concerning MED. However, MED has proven it's safety and efficiency in multiple studies [4,9-15]. Three of these studies have compared MED with conventional open discectomy [10,12,13], 1 was randomised [12]. There is a trend towards faster recovery and less tissue damage in MED, although due to limited number of patients and methodological flaws, no firm evidence based conclusions can yet be drawn.

The rational of MED is a muscle-splitting approach by using sequential dilators and insertion of a tubular retractor, instead of subperiostal muscle dissection in the conventional open procedure. Iatrogenic devascularisation and denervation of paraspinal muscles is regarded to be one of the causes of poor clinical outcome and failed-back-surgery syndrome [16]. Therefore, the muscle-splitting technique of MED is expected to result in less tissue damage since subperiostal muscle dissection is prevented. However, 1 study of 40 patients failed to show a significant difference in post-operative contrast enhanced magnetic resonance imaging (MRI) with respect to paraspinal muscle damage between MED and conventional open discectomy [11].

Another parameter to analyse post-surgery tissue damage is serum creatine kinase (CK) as indicator of muscle injury. CK increases after spinal surgery and reaches a maximal value 1 day after surgery [17]. Nakagawa et al. have compared CK values on day 1 after MED and conventional open discectomy. They showed a significant difference in postoperative CK in favor of the MED [10]. Whether this is related to clinical outcome is not known.

Minimally invasive spine surgery has limitations as well. One of the disadvantage of MED is potential nerve root injury because of limited exposure. On the contrary, it is shown that MED causes less intraoperative nerve root irritation compared to conventional surgery [12].

Another issue related to limited exposure is recurrent disc herniation. The recurrence rate after MED is not known but it is expected to be higher than after conventional open discectomy since less disc material is retrieved. However, a recent randomised trial has shown superiority of sequesterectomy only, compared to conventional discectomy with regard to recurrence rate [18]. Therefore, the relationship between the extent of disc retrieval and recurrence rate is debated. In our study we will weight the total amount of disc retrieval in both surgical techniques and correlate this with disc recurrency.

Like other new minimally invasive techniques, MED has a learning curve which is related to surgery time, complications, conversion to the open procedure, and recurrent disc herniation. It is demonstrated that a surgeon should perform at least 30 procedures in order to be skilled and know the pitfalls [14]. Skill acquisition of MED is necessary before clinical assessment of MED versus conventional open discectomy can be started. Therefore, in our trial we have selected surgeons with large experience in MED.

Presently, the golden standard in surgical treatment of lumbar disc herniation is the unilateral transflaval discectomy to which all other techniques should be compared. The purpose of our study is to assess whether MED is more (cost)-effective than conventional open discectomy. The cost-effectiveness results will be a trade-off between a quicker relief in leg pain in the MED group versus the advantage of lower costs in the conventional group. Moreover, we will identify possible subgroups of patients who will substantially benefit from one of the allocated surgical treatments. Since MED is hypothesised to have a particularly favorable short term effect, we will set 8 weeks and 1 year as primary measure points.

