### Sample size

The sample size is calculated on the basis of the Roland Disability Questionnaire for Sciatica. A difference in effect between MED and open discectomy is assumed whenever MED will obtain at least 20% difference in Roland score at 8 weeks after randomisation. Conventional open discectomy is assumed to have at least 60% good result 8 weeks after surgery. This means that MED is proven to be more effective than conventional surgery whenever 80% or more of the patients have a good outcome 8 weeks after surgery. The numbers used for this sample size are drawn from the Maine Lumbar Spine Study 1 year and 5 year results and were discussed in detail recently [19,21].

This trial attempts to enroll 300 patients with lumbar disc herniations (150 patients in both treatment groups, including 8% loss to follow-up) which is regarded sufficient to detect a difference of 20% (α = 0,05 and a power of 90%) in the primary outcome.

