### Statistical analysis

Baseline comparability will be analysed by descriptive statistics to determine whether randomisation was successful. Whenever necessarry, adjustments for baseline variables will be performed in the analysis. Differences in outcome measures between both groups, together with 95% confidence intervals, will be calculated. Besides a difference in recovery between the two groups, analysis of a difference in time to recovery will be carried out as well. All data are analysed according the "intent-to-treat principle". In addition, an explorative subgroup analysis is conducted to investigate whether the treatment effect varies over specific subgroups of patients (table 3). Data will be stored via the internet-based secure data management system "ProMISe" of the department of Medical Statistics and Bioinformatics. The analyses will be carried out using appropriate statistical software (e.g. SPSS).

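### Two time points are called primary, but size and success are defined at 8 weeks only and nothing says which one decides

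*Protocol article*

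**What the plan says.** Two places in the protocol article give the primary outcome two time points of equal rank. The abstract (Methods/Design) describes functional assessment "measured by the Roland Disability Questionnaire for Sciatica, at 8 weeks and 1 year after surgery". The Background says "we will set 8 weeks and 1 year as primary measure points". The opening of the Methods/Design section also directs the analysis at recovery in both the short and the long term.

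The Sample size section is written for one of them. The control rate is an 8-week rate: "Conventional open discectomy is assumed to have at least 60% good result 8 weeks after surgery". The only success criterion in the article is also at 8 weeks: "MED is proven to be more effective than conventional surgery whenever 80% or more of the patients have a good outcome 8 weeks after surgery". Alpha appears once, where 300 patients are said to be enough to "detect a difference of 20% (α = 0,05 and a power of 90%) in the primary outcome". It is not given per time point, and sidedness is not stated.

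The Outcome assessment section expects an advantage for microendoscopic discectomy (MED) in the short term and comparable results at 6–12 months. The Statistical analysis section says: "Differences in outcome measures between both groups, together with 95% confidence intervals, will be calculated". It gives no order of testing, no adjusted level, and no rule on whether one or both time points must succeed.

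**The concern.** These statements do not fit together. Two sections make 8 weeks and 1 year equally primary. The sample size, the success criterion and the short-term rationale point to 8 weeks alone. One year is called primary but has no assumed rates, no success criterion and no superiority hypothesis.

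The article itself predicts the case in which this matters: a difference at 8 weeks and none at 1 year. As written, a reader cannot tell whether that is a positive trial, a mixed one, or one judged on 8 weeks only. The reverse case, a difference at 1 year without one at 8 weeks, could also be presented as a primary finding. If both routes are open at the full 0.05, the chance of a false primary claim exceeds the stated 5%.

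**Working it through.** **Inputs.** From the Sample size section: 60% versus 80% good outcome at 8 weeks, alpha 0.05, power 90%, 150 per arm including 8% loss, so 150 × 0.92 = 138 evaluable per arm. Assumed, because the article does not give them: two-sided tests, and the correlation ρ between the 8-week and 1-year test statistics (range 0 to 0.9).

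**1. The plan's own figure.** Per arm, n = [z(1−α/2)·√(2·0.7·0.3) + z(0.90)·√(0.6·0.4 + 0.8·0.2)]² / 0.2².

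- Two-sided 0.05: (1.960 × 0.648 + 1.282 × 0.632)² / 0.04 ≈ 108.2, so 109. Then 109 / 0.92 gives 119 per arm, 238 in total.
- The same with continuity correction: 119, then 130 per arm, 260 in total.
- One-sided 0.05: 194 in total, or 214 with continuity correction.
- Two-sided 0.025: 129, then 141 per arm, 282 in total.
- Two-sided 0.025 with continuity correction: 138, then 150 per arm, 300 in total.

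The stated 300 does not follow from alpha 0.05. It is larger than needed there, so calling it sufficient is not wrong. It equals the continuity-corrected size at 0.025.

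**2. Error if either time point suffices at two-sided 0.05.** The family-wise error is 1 − P(|Z₁| < 1.96 and |Z₂| < 1.96) under a bivariate normal. At ρ = 0 this is 1 − 0.95² = 9.75%. The last column counts only false claims in favour of MED, for which a single test has 2.5%.

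| Assumed ρ | Both directions | Favouring MED only |
|---|---|---|
| 0 | 9.75% | 4.9% |
| 0.5 | 9.1% | 4.5% |
| 0.7 | 8.3% | 4.2% |
| 0.8 | 7.8% | 3.9% |
| 0.9 | 7.0% | 3.5% |

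**3. Error if one rule is written.** With 8 weeks alone deciding, or 8 weeks first and 1 year only after success, it is at most 5%. With 0.025 at each time point it is 4.9% at ρ = 0 and 3.6% at ρ = 0.9.

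**4. Power at 8 weeks with 138 per arm.** The standard errors are √(0.42/138) = 0.0552 under the null and √(0.40/138) = 0.0538 under the alternative.

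- Two-sided 0.05: Φ[(0.2 − 1.960 × 0.0552) / 0.0538] = 95.6%. Subtracting 1/138 from the difference as a continuity correction gives 94.2%.
- Two-sided 0.025: Φ[(0.2 − 2.241 × 0.0552) / 0.0538] = 92.2%, or 90.0% with the correction.

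Power at 1 year cannot be computed, because the article gives no 1-year rates.

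**The case against.** The strongest reply is that the article already points to 8 weeks. The effect size, both rates and the only success criterion are set there, and comparability is expected later, so a superiority claim from 1 year alone is not clearly planned. On that reading the error is 5%. This stands as a limit on the size of the problem. It does not remove the problem, because the abstract and the Background name both times as primary without ranking them.

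A reader might infer that each time point will be tested at 0.05, so that the true error is 8–10%. The article does not support that as a fact. Alpha is stated once, for the primary outcome as a whole, and the sentence on 95% intervals concerns estimates and names no time points. The inflated figure holds only if either result suffices at full alpha. Even then it depends on an assumed correlation and on counting false claims in both directions.

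It can also be said that an alpha split is already built in, since 300 matches the size at 0.025. That is possible, but it may equally be coincidence or rounding up. If a split was intended, it is unwritten and the stated alpha does not match it.

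Finally, this is a condensed article, and adjustment methods commonly sit in an analysis plan that is not shown. The mechanics can be left there. Which time point defines a positive trial is a design statement that this article makes, and makes inconsistently.

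**Conclusion.** The point holds as a mismatch within the article: two time points are labelled primary, while size, success and hypothesis are set for one, and no statement says which decides. The consequence is conditional. If either time point can carry a primary claim at two-sided 0.05, the family-wise error is about 7–10% for an assumed correlation of 0.9 to 0, or 3.5–4.9% for false claims favouring MED. If 8 weeks alone decides, it is 5%. The article does not settle which case applies, so an error rate above 5% is a risk that the text leaves open and not an established property of the trial.

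**What to change.** State one rule, and settle it before any unblinded data are seen.

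- **Preferred.** Name RDQ recovery at 8 weeks as the single confirmatory test at two-sided 0.05, and test 1 year only if it succeeds. This fits the short-term hypothesis and the Sample size section, and it gives 95.6% power at 8 weeks (94.2% with continuity correction). The cost is that a 1-year difference without an 8-week difference is not a primary claim, whatever its p value.
- **Alternative.** Keep both time points as primary, test each at two-sided 0.025 (Bonferroni) with 97.5% intervals, and state alpha 0.025 in the Sample size section, where it reproduces 300 with continuity correction. Power at the 8-week rates is 90–92%. The cost is that a lone result with p between 0.025 and 0.05 at either time point is not a primary claim. Rates for 1 year would have to be stated before power could be claimed there.

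The abstract, Background, Sample size and Statistical analysis sections should then describe the time points in the same way. Either option takes a sentence or two and no additional patients.

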## Methods/Design

We designed an observer and patient blinded randomised cost-effectiveness trial in the treatment of lumbar disc herniation in which two surgical techniques are compared in a parallel group design. The primary outcome measure is the Roland Disability Questionnaire for Sciatica. The follow-up period will last 2 years. In order to collect enough patients, a multi-center design is necessary. The study protocol was approved in all participating hospitals.

Our primary question is whether MED is more (cost)-effective than open discectomy. The analysis will be focused on the proportion of patients who are recovered to a normal functional situation at the short and long term. Moreover, we want to identify certain subgroups who may benefit more of one of the allocated treatments.

### Patients

All patients between 18 and 70 years with sciatica lasting more than 6–8 weeks are eligible for this study. Imaging studies (MRI) must confirm a herniated disc larger than 1/3 of the spinal canal diameter (figure 1), or a smaller herniated disc with concomitant lateral recess stenosis or sequestration. Additional inclusion and exclusion criteria are listed in table 1. Patients with small herniated discs less than 1/3 of the spinal canal diameter are eligible for our parallel study of percutaneous laser discus decompression (PLDD) which compares PLDD with conventional discectomy. This trial will be discussed seperately.

Patients are referred by a neurologist with MRI and conventional imaging of the lumbar spine. During the first visit to the neurosurgical outpatient clinic, the patient's history and a standard neurological examination will be documented. Conform our selection criteria, the neurosurgeon decides whether a patient is eligible for the MED trial. The study will be explained to the patient and, in case of a positive reaction, an appointment is made with one of the research nurses. Because the patient needs some time to consider participation, the first visit to the research nurse is planned after at least 2 days. After informed consent, the questionnaires, outcome measures and baseline variables are recorded.

### Randomisation procedure

Patients will be randomly allocated to either MED or conventional discectomy. Randomisation will take place on the operating room within 4 weeks after the first visit to the research nurse. A randomisation list is prepared for every participating hospital-nurse combination. Variable-sized blocks of random numbers are formed to ensure equal distribution of the randomisation treatments over hospitals and research nurses. The data manager at the department of Biostatistics, who is not involved in the selection and allocation of patients, will prepare coded, sealed envelopes containing the treatment allocation. In the operating room, after induction of anesthesia, the surgeon will open the envelope and the allocated treatment is performed. Patients and research nurses are kept blinded for the allocated treatment during the follow-up period of 2 years.

### Intervention

Patients will be randomised into conventional unilateral transflaval discectomy (A) or MED (B). Depending on the surgeon and patient's preference, surgery will be performed under general or spinal anesthesia. The patients will be positioned prone and the affected disc level is verified with fluoroscopy. The participating surgeons have large experience in both techniques. A standardized Case Record Form (CRF) will register the surgeon's findings and this CRF, together with the randomisation envelope, will be returned to the data center in a sealed envelope.

### (A) Unilateral transflaval discectomy

A small midline incision (2–3 cm) will be made and the paravertebral muscles will be discected unilaterally. Laminotomy will be performed when necessary. In order to decompress the nerve root, the herniated disc will be removed as much as possible through a unilateral transflaval approach. All retrieved disc material will be collected and weighted afterwards. The wound will be closed in layers with a suction drain when necessary. Patients will be operated with loupe magnification or microscope depending on the surgeon's preference.

### (B) Microendoscopic discectomy

The same size midline incision will be made, the skin will be retracted laterally and the guidewire and sequential dilators will be placed paraspinal under lateral fluoroscopy control. The tubular retractor will be connected to a flexible arm and fixed. Under microscopic view a unilateral flavectomy and discectomy will be peformed. All removed disc material will be collected. The wound will be closed in layers with a suction drain when necessary. Whenever MED will be converted to an open discectomy, the patient will maintain in group B conform the 'intent to treat'principle.

Surgery will take place within 4 weeks after inclusion on the outpatient neurosurgical clinic. Hospital admission will be 2–7 days (including the day of admission), depending on the usual care of the participating hospital. During the immediate post-operative period the patients will be mobilised as soon as possible with the help of a physiotherapist. Attempts will be made to discharge the patient as soon as possible in both study groups. The physician who will discharge the patient is not aware of the performed treatment. Patients and their guided physiotherapists are stimulated to resume homeactivities and work as soon as possible.

### Baseline data

The baseline questionnaire assesses demographics, hobbies, sports, work status, smoking status, back pain history, family history of sciatica, co-morbidity, weight and length. The patient's satisfaction at work will be registered. The treatment preference of both patient and surgeon will be assessed on a 5-point scale ranging from "strong preference for conventional open discectomy" to "strong preference for MED". Moreover, the expected recovery 8 weeks after surgery of both patient and surgeon will be registered.

### Outcome assessment

We will use the below described validated outcome parameters which will be assessed by means of questionnaires. Follow-up examinations by the research nurse will take place 4, 8, 26 and 52 weeks after randomisation. Patients will be neurologically examined and questionnaires will be filled in (table 2). In between at 1, 2, 6, 12, 38, 78 and after 104 weeks the main questionnaire (primary outcome measures) will be filled in at home and send to the data center. The outpatient control by the neurosurgeon will be at 8 weeks and more if necessary.

We hypothesise a difference in (cost)-effectiveness between MED and conventional discectomy in favor of the MED on the short term, and comparable (cost)-effectiveness after 6–12 months. Therefore the main questionnaire will be answered at 8 weeks and 1 year after surgery.

